### Outcome assessments

2.8

#### Primary results

2.8.1

The primary outcome, assessed within 2 years post-discharge, is defined as the treatment rates of anti-osteoporotic drugs among patients receiving pharmacist-led interventions compared to those on conventional treatment. The treatment rates are calculated as the ratio of patients who still use anti-osteoporotic drugs to the total number of enrolled participants.

Ongoing treatment is defined as the uninterrupted use of anti-osteoporotic medications, where any treatment interruption lasting more than 60 days is considered as discontinuation (21). According to previous studies, interruptions in osteoporosis treatment exceeding this duration are associated with an increased fracture risk and reduced treatment efficacy (7, 22).

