### Regular follow-up and engagement

2.7

Participants who did not take the medication as scheduled beyond 8 weeks of the expected follow-up period, as well as those who no longer wish to participate in the study, were discontinued from the study.

To address the potential for missing data due to the high dropout rate in the elderly population, we will incorporate an intention-to-treat (ITT) analysis approach. ITT analysis will include all randomized participants in the analysis according to their assigned group, regardless of whether they completed the follow-up or not, which may minimize the bias introduced by missing data and provide a conservative estimate of the treatment of the treatment effect (6).

Participants will be followed up at 1 week, 1 month, 3 months, and then every 3 months thereafter for a total of 24 months. This frequent and structured follow-up schedule is designed to enhance participant retention and ensure comprehensive data collection.

Multiple follow-up methods, including telephone interviews, pharmaceutical clinic visits, and pharmacy practice in e-hospitals, will be used to accommodate different preferences and accessibility of elderly patients.

Trained pharmacists will conduct telephone interviews to gather detailed information on medication use, adverse reactions, falls, and fracture events. Face-to-face consultations at the pharmaceutical clinic will provide personalized medication education and counseling, addressing patient questions and offering the necessary support. For patients unable to visit the clinic, real-time pharmacy practice in e-hospitals via video conferencing or instant messaging will ensure timely information and support.

To ensure comprehensive coverage and maintain data quality, all research staff involved in data collection, including pharmacists and clinic personnel, underwent comprehensive training on the study protocol, data collection methods, and the use of standardized tools. Additionally, we involved family members or caregivers in the follow-up process to provide accurate information on participants’ conditions and medication adherence, ensuring complete and reliable data.

To encourage participant retention, educational materials and personalized support were provided during each follow-up session.

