**Figure 3 fig3:**
[figure not shown]
Surgical pharmacist-led intervention pathway of this study.

All counting data will be analyzed using the Statistics Package for the Social Science (SPSS) program, version 23.0. Continuous variables are expressed as mean or median (quarterly distance) with standard deviation (mean ± SD), and categorical variables are expressed as frequencies or percentages. The *t*-test will be used to compare continuous data that satisfies normal distribution or the Willcoxon test will be performed for the skewed distribution data. The chi-squared test or Fisher’s exact test will be used to assess the comparison of categorical data in different groups.

For outcomes such as continued treatment rates of anti-osteoporotic drugs, Kaplan–Meier curves will be used to characterize how the probability of an endpoint event changes with survival time, and comparisons between survival curves will be carried out using log-rank tests. We used the Cox proportional hazards model to estimate the hazard ratios and 95% confidence intervals. Missing observations were accounted for using the predictive mean matching (PMM) method. If the missing data are numerical, it will be filled by predictive mean matching; meanwhile, if the missing data are non-numerical, logistic regression and discriminant functions will be used to fill it. The *p*-value threshold is 0.05 (*p* < 0.05), and a p-value below this threshold indicates that the difference is statistically significant.

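### The time-to-event analysis of continued treatment has no rule for patients who never start, and each available reading departs from the primary ratio

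*Protocol article*

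**What the plan says.** Section 2.8.1 defines the primary treatment rate as "the ratio of patients who still use anti-osteoporotic drugs to the total number of enrolled participants". It adds: "Ongoing treatment is defined as the uninterrupted use of anti-osteoporotic medications", with the qualification that "any treatment interruption lasting more than 60 days is considered as discontinuation".

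Section 2.11 lists chi-squared or Fisher tests for categorical data in general. It then turns to this outcome by name: "For outcomes such as continued treatment rates of anti-osteoporotic drugs, Kaplan–Meier curves will be used", "comparisons between survival curves will be carried out using log-rank tests", and "We used the Cox proportional hazards model to estimate the hazard ratios and 95% confidence intervals". It gives no time origin and no event rule beyond the 60-day interruption.

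Two statements define who is analysed. Section 2.7 says that "ITT analysis will include all randomized participants in the analysis according to their assigned group". Section 2.11 limits the ITT population to randomised patients who took at least one dose of drugs. Section 2.7 also removes from the study patients who have not taken medication as scheduled for more than 8 weeks.

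Initiation of therapy is a separate secondary outcome (section 2.8.2), and no initiation rate is assumed for either arm.

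**The concern.** The ratio and the survival analysis address the same outcome but need not score the same patient alike. A never-starter is in the denominator of the ratio and not in the numerator, so fails. In the survival analysis, an interruption requires earlier use, so the one stated event cannot happen to that patient.

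Never-starters are likely to be common. The Introduction cites 27.7% of women treated within 12 months of a fracture, and 20% of elderly Chinese hip-fracture patients treated appropriately. The intervention includes drug recommendations to orthopedists and individual osteoporosis treatment plans (sections 2.6.1 and 2.6.2), so it may raise initiation. A patient who starts becomes able to have a discontinuation event. An arm that starts more patients can therefore collect more events while keeping more patients on treatment. The log-rank test and hazard ratio could then understate, miss or contradict a real gain in the primary ratio.

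**Working it through.** **Inputs from the article.** Continued-treatment rates of 30% (control) and 50% (intervention), two-sided 5% level, 80% power, 20% dropout, 91 then 114 per group (section 2.10); 24 months of follow-up (section 2.7).

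**Assumptions.** The 30% and 50% are read as month-24 rates among all randomised patients. Initiation s by arm is not given, so a range is used. Starters begin at discharge and stop at a constant hazard. There are 91 evaluable patients per arm and no other loss.

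**Step 1: the plan's own figure.** For two proportions with unpooled variance, n = (1.96 + 0.8416)² × (0.50×0.50 + 0.30×0.70) / 0.20² = 7.849 × 0.46 / 0.04 = 90.3, so 91. Then 91 / 0.80 = 113.75, so 114 per group and 228 in total. This agrees with section 2.10. The trial is therefore sized for a comparison of two proportions, not a log-rank test. A pooled two-proportion test with 91 per group has 79% power, whatever the initiation rates.

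**Step 2: one never-starter under each passage.**
- Ratio in 2.8.1: failure.
- All-randomised set of 2.7 with the 60-day event rule: no event.
- One-dose set of 2.11: excluded, if the dose means an anti-osteoporotic drug.
- 8-week rule of 2.7: censored near day 56 (8 × 7), if the rule covers patients who never started.

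**Step 3: formulas.** Let P be the month-24 rate.
- No event: event-free share = 1 − s + P. The arm difference is 0.20 − (s_int − s_ctl), which is zero at a 20-point initiation gain and negative above it.
- Excluded: share of starters still on drug = P / s, and HR = ln(P_int / s_int) / ln(P_ctl / s_ctl). For 50% vs 70% initiation, 0.30/0.50 = 0.60 and 0.50/0.70 = 0.714, so HR = 0.66.
- Event at time zero: the month-24 curves are 30% and 50% for any s.

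**Step 4: simulated log-rank results.** There were 1,000 runs per scenario. Paired log-rank entries are the % of runs significant for intervention / for control. In the time-zero column no run was significant for control.

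| Initiation, control vs intervention | Event-free share if no event | No event | Starters only: HR | Starters only | Censored at 8 weeks | Event at time zero |
|---|---|---|---|---|---|---|
| 80% vs 80% | 50% vs 70% | 81 / 0 | 0.48 | 87 / 0 | 87 / 0 | 75 |
| 60% vs 70% | 70% vs 80% | 36 / 0 | 0.49 | 68 / 0 | 67 / 0 | 77 |
| 50% vs 70% | 80% vs 80% | 3 / 3 | 0.66 | 27 / 0 | 21 / 0 | 83 |
| 60% vs 80% | 70% vs 70% | 3 / 2 | 0.68 | 33 / 0 | 27 / 0 | 86 |
| 40% vs 70% | 90% vs 80% | 0 / 48 | 1.17 | 1 / 6 | 1 / 7 | 86 |
| 40% vs 80% | 90% vs 70% | 0 / 94 | 1.63 | 0 / 24 | 0 / 30 | 91 |

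In every row the true month-24 rates are 30% and 50%.

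**The case against.** A reader might infer that the protocol scores never-starters as continuing to month 24. The article does not support that. No passage says so, the definition of ongoing treatment requires use, and the primary ratio counts such a patient as a failure. The one-dose set may exclude them, and the 8-week rule may remove them early. The columns with 48% and 94% of runs favouring control therefore show one possible reading, not the stated plan.

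A reader might also infer that log-rank or Cox is the sole primary test. Section 2.11 does not name one, and the chi-squared test that it lists could be applied to the ratio. Nor does the article say that the intervention works mainly through initiation: education on persistence, monitoring of adverse reactions and repeated follow-up also aim at continuation. Finally, event coding and time origin are often left to an analysis plan, which is not shown here.

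These points stand, and they lower the severity. They do not remove the concern. The two ITT statements conflict within the article. Section 2.11 sends this outcome by name to survival methods. The alternatives to no-event scoring also lose most of the planned power at a 20-point initiation gain, so excluding or censoring never-starters does not restore agreement with the ratio.

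**Conclusion.** The point holds as an unresolved conflict between the primary ratio, the single event rule and the two population statements. It does not show that the plan fixes a wrong score for never-starters.

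Its size depends on an initiation gain that the article does not give. At equal initiation there is no harm. A 10-point gain already costs power under each of the three readings. At 20 points the effect is lost under no-event scoring (about 3% of runs favour the intervention) and much weakened under the other two (21% to 33%). At 30 points it reverses under no-event scoring and is essentially lost under the other two. At 40 points all three can give significant results for control. The figures assume a constant stopping hazard, starting at discharge and no other loss.

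It should be settled before outcome data are analysed, because the choice of reading can change the direction of the result.

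**What to change.** 1. In sections 2.8.1 and 2.11, name the primary test: the difference in on-treatment proportions at month 24 among all randomised patients, with never-starters counted as not on treatment. This matches the 2.8.1 ratio and the section 2.10 calculation, and it scores late starters correctly.
2. Keep Kaplan–Meier and log-rank as supportive, with time from discharge and never-starters as events at time zero.
3. Do not rely on the Cox hazard ratio for this outcome, because a block of failures at time zero breaks proportional hazards.
4. Reconcile the all-randomised statement in 2.7 with the one-dose statement in 2.11, and say how patients who meet the 8-week rule are scored.

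The cost is a few sentences. The month-24 test needs only drug-use status at a visit that is already scheduled. There are two small downsides. The hazard ratio is no longer the main summary. The supportive curve still misstates late starters: a patient who starts at month 4 and continues is on treatment at month 24, but a curve that begins at discharge can only fall.

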ADRs documented in the Case Report Form (CRF) were systematically monitored and recorded through self-reporting during follow-up interviews, clinic visits, and the review of electronic health records. Additionally, pharmacists conducted regular medication reconciliations to identify potential ADRs and provided management recommendations (26).

The Treatment Satisfaction Questionnaire for Medication version II (TSQM-II) was administered to assess patient’s treatment satisfaction (22). This validated tool assesses patient satisfaction across various areas, including effectiveness, side effects, and convenience.

### Data collection and management

2.9

The baseline information was gathered, including (1) basic information: age, sex, body mass index (BMI), smoking history, alcohol intake, medical insurance; (2) disease history; (3) primary diagnosis at hospitalization, fracture sites, results of BMD assessments, and anti-osteoporotic drugs; (4) laboratory results: serum creatinine, hemoglobinosinase, cottage transaminase, serum albumin, C-terminal Telopeptide of Type I Collagen (CTX), N-terminal Propeptide of Type I Collagen (P1NP), BMD; (5) surgery-related information: type of surgery, surgical incision, surgical operation category, anesthesia method, American Anesthesiologist Association (ASA) score, surgical level, surgical duration, incision healing category; and (6) other drugs used during hospitalization.

During the intervention, dynamic data collection focused on key aspects as follows: the anti-osteoporosis drug regimen and other long-term medications used by patients prior to admission, any drug allergies, the outcomes of medication reconciliations and physician recommendations, treatment satisfaction assessed via TSQM-II, ADRs, and the incidence of new fractures during follow-up.

To ensure comprehensive coverage and maintain data quality, all research staff involved in data collection, including pharmacists and clinic personnel, will undergo comprehensive training on the study protocol, data collection methods, and the use of standardized tools. Regular communication with participants through multiple channels (telephone, email, and clinic visits) will be maintained to ensure thorough engagement (18). Participants will also receive personalized support, along with flexible follow-up options and reminders to ensure they remain engaged in the study. Information obtained through telephone interviews will be compared with data from clinic visits and pharmacy practices in e-hospitals to identify any discrepancies.

### Sample size

2.10

The sample size estimation was determined by measuring a clinically significant difference in the primary outcome—continued treatment rates of anti-osteoporotic drugs between the intervention and control groups. To achieve a statistical power of 80% (β = 0.20) with a significance level of α = 0.05 (two-sided), we conducted a sample size calculation using the following assumptions.

Based on previous studies, we assumed a continued treatment rate of 50% in the intervention group (P1) and 30% in the control group (P2) (1, 7). Considering the potential high dropout rate among the older adult population, we accounted for a 20% dropout rate over the 2-year follow-up period. The calculation resulted in a required sample size of 91 participants per group. Considering a 20% dropout rate, we adjusted the sample size to 114 participants per group, resulting in a total sample size of 228 participants. The sample size is calculated by PASS15.0 software, and the calculation equation is shown in Figure 1.

**Figure 1 fig1:**
[figure not shown]
The calculation formula of sample size in this study.

### Statistical analysis

2.11

The statistical analysis will be along with the intention-to-treat (ITT) principles. The ITT population will include patients who meet the criteria, are randomized, and take at least one dose of drugs after being enrolled (Figures 2, 3).

**Figure 2 fig2:**
[figure not shown]
Flow diagram of the study.

**Figure 3 fig3:**
[figure not shown]
Surgical pharmacist-led intervention pathway of this study.

All counting data will be analyzed using the Statistics Package for the Social Science (SPSS) program, version 23.0. Continuous variables are expressed as mean or median (quarterly distance) with standard deviation (mean ± SD), and categorical variables are expressed as frequencies or percentages. The *t*-test will be used to compare continuous data that satisfies normal distribution or the Willcoxon test will be performed for the skewed distribution data. The chi-squared test or Fisher’s exact test will be used to assess the comparison of categorical data in different groups.

For outcomes such as continued treatment rates of anti-osteoporotic drugs, Kaplan–Meier curves will be used to characterize how the probability of an endpoint event changes with survival time, and comparisons between survival curves will be carried out using log-rank tests. We used the Cox proportional hazards model to estimate the hazard ratios and 95% confidence intervals. Missing observations were accounted for using the predictive mean matching (PMM) method. If the missing data are numerical, it will be filled by predictive mean matching; meanwhile, if the missing data are non-numerical, logistic regression and discriminant functions will be used to fill it. The *p*-value threshold is 0.05 (*p* < 0.05), and a p-value below this threshold indicates that the difference is statistically significant.

### Ethics issues

2.12

Ethical approval was obtained before the start of this protocol from the Committee of Ethics of the First Affiliated Hospital of Shantou University Medical College (approval number: B-2023-194). The study protocol adheres to the principles outlined in the Declaration of Helsinki and complies with all relevant national and institutional guidelines for research involving human participants.

Written informed consent was obtained from all participants. The content form detailed the study objective, procedures, risks, and benefits. Participants were able to withdraw from the study and/or the collection of linked data at any time. Verbal explanations were provided to ensure understanding, and signed forms were securely stored. Participant’s privacy was protected through data anonymization and secure storage. Data were coded with unique identifiers, stored in password-protected databases, and were accessible only to authorized personnel. All staff were required to sign confidentiality agreements, and data sharing adhered to relevant regulations.

## Discussion

3

This study implements a pharmacist-led intervention to evaluate its effectiveness in the treatment of osteoporotic fractures. Findings from this present study assume that the involvement of pharmacist-led interventions in osteoporotic fracture therapy management will improve anti-osteoporotic drug treatment rates and medication adherence, further decreasing the risk of refracture among Chinese patients with osteoporotic fractures.

To our knowledge, this is the inaugural prospective study to focus on the role of surgical pharmacists in the medication management of osteoporotic fractures in China, with an emphasis on treatment outcomes, prognosis, and medication adherence.

Osteoporotic fracture, a common consequence secondary to osteoporosis (27), results in more socioeconomic burdens than other chronic diseases, such as hypertension, asthma, and rheumatoid arthritis. A previous study has shown that older adults tend to have a higher risk of osteoporosis and further suffer from a secondary fracture, especially in postmenopausal women and men aged above 50 years (6). There is still a gap in osteoporosis treatment, causing a low treatment initiation rate among the elderly, as a result of the lack of awareness of osteoporosis and medication adherence (10).

Several studies have demonstrated that pharmacists should be uniquely positioned in osteoporotic fracture management and contribute to addressing the osteoporosis treatment gap (28). Interventions constructed by pharmacists have exhibited an effect in enhancing osteoporosis management, including medication interviews, patient education and counseling, cooperation with physicians or nurses, and risk assessment of refracture. Pharmacist-led interventions were identified to enhance not only BMD testing and calcium intake but also promote the use of vitamin D supplements and the initiation of osteoporosis treatments (26, 29–32), in addition to medication adherence to anti-osteoporotic drugs. Population screening for patients at a higher risk of fracture is essential for pharmacists to increase osteoporosis treatment rates and reduce the incidence of refractures (33).

A specific medication reconciliation focusing on reduction in falls and subsequent fractures, as well as drug-associated secondary osteoporotic fracture, was recommended by international and Australian osteoporosis management guidelines, if possible (2). Despite a clinical trial demonstrating the effectiveness of medication reconciliation in optimizing medication management for patients with minimal trauma fractures (34), no exact routine of pharmacist-led medication reconciliation has been established. A follow-up interview by pharmacists plays a crucial role in ensuring continuity of care and medication compliance.

Therefore, in this present study, a surgical pharmacist-led intervention was designed for patients with osteoporotic fracture, which contained medication interviews, patient education, counseling, monitoring of potential adverse drug reactions, and up to 10 follow-ups within 24 months. Participants were reminded of tailored precautions for taking medications using telephone interviews, pharmaceutical clinics, and pharmacy practices in e-hospitals, to support adherence to anti-osteoporotic drugs.

There are some limitations to this study. First, only a relatively single center was involved in this study, which means the results may not be representative of all patients with OF. Second, older participants may contribute to a high dropout rate due to physical decline or death. As a result, there is a risk of missing data during follow-up due to these drop-outs. External validations are needed to further investigate the detailed models and roles of surgical pharmacists in the management of therapy and medication compliance of patients with OF.

In conclusion, our results are likely to provide deeper insights into the association between pharmacist-led interventions and medication treatment and adherence to anti-osteoporotic drugs in Chinese elderly patients with osteoporotic fractures. This study will provide valuable data for developing a potential pharmaceutical service model and a longitudinal follow-up visit for patients with OP, aiding in establishing individual intervention and treatment strategies.
